### Primary outcome

The primary outcome is complication within the 12-month post-operative period. These complications are defined in Table 2. Non-union will be assessed at the radiocarpal, midcarpal and carpometacarpal joint (if arthrodesed) by CT.

**Table 2 Tab2:** Complications will be defined to include the following

Wound dehiscence	
Infection: superficial (treated with antibiotics alone) and deep (requiring surgical debridement and antibiotics	
Fracture: in the perioperative period and in the follow up period	
Non-union: recorded radiocarpal, midcarpal and carpometacarpal joint and defined as absence of bridging bony trabeculae with no interval change over 3 months	
Hardware breakage: plate or screw, managed operative or non-operatively	
Tendon rupture	
Tendon irritation: requiring treatment	
Complex regional pain syndrome: defined according to Budapest criteria	
Nerve injury: operatively or not operatively managed	
Other: medical and surgical	

### Secondary outcomes

Secondary outcomes will include changes from baseline DASH and PRWE. Secondary outcomes will also include patient satisfaction, grip strength and late complications.

The DASH questionnaire is used to assess global disability of the upper limb. The questionnaire is a self-reported 30 item questionnaire that patients rate difficulty and interference with daily life on a 5-point Likert scale. The DASH is scored using the formula = ([(sum of n responses)/n] -1) where n represents the number of completed items. The score on both test ranges from 0 (no disability) to 100 (most severe disability).

The PRWE is a wrist specific questionnaire that has 15-items designed to measure wrist pain and disability in activities of daily living. The pain subscale contains 5 items each of which is further rated from 1 to 10. The function subscale contains a total of 10 items which are further divided into 2 sections: specific activities (6 items) and usual activities (4 items). Both subscales are scored out of 50, and the total score is the sum of the two scores, where 100 is the poorest possible outcome.

Grip strength will be recorded from three attempts alternating between left and right hands have using Jamar digital dynamometer in position 2.

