### Statistical analysis

All statistical analysis will be performed by a statistician blinded to treatment.

We choose a superiority study design, with the assumption that treatments are equivalent and set out to test this hypothesis. The primary outcome of complications will be analysed by proportional analysis (odds ratio). Continuous secondary outcomes will be analysed by ANOVA. This study is not powered to discriminate between treatments in terms of DASH and PRWE given the MCID (95% confidence interval) is 10 [5–15] and 14 (8–20), respectively [14].

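### The DASH formula as printed spans 4 points, not the stated 0 to 100, because a multiplier of 25 is missing

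*Protocol article*

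**What the plan says.** Change from baseline in DASH and PRWE is a secondary outcome. The Secondary outcomes section describes the DASH as a "self-reported 30 item questionnaire that patients rate difficulty and interference with daily life on a 5-point Likert scale" and gives the scoring rule: "The DASH is scored using the formula = ([(sum of n responses)/n] -1) where n represents the number of completed items". The next sentence reads "The score on both test ranges from 0 (no disability) to 100 (most severe disability".

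For the PRWE, the same section says "The pain subscale contains 5 items each of which is further rated from 1 to 10". It then says "The function subscale contains a total of 10 items which are further divided into 2 sections: specific activities (6 items) and usual activities (4 items", without a rating range for the function items, and ends with "Both subscales are scored out of 50, and the total score is the sum of the two scores, where 100 is the poorest possible outcome".

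The Statistical analysis section assigns continuous secondary outcomes to ANOVA. It says the trial is not powered for DASH or PRWE, "given the MCID (95% confidence interval) is 10 [5–15] and 14 (8–20), respectively".

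**The concern.** The DASH formula and its range stand in adjacent sentences and cannot both be right. The mean of five-point items, less 1, cannot come near 100. The MCID in the Statistical analysis section belongs to the 0 to 100 scale, so two statements in the article disagree with the formula.

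At stake is the scale on which a named secondary outcome is reported at 1, 2 and 5 years. Because the trial is not powered for the DASH, readers will rely on the size of the estimated difference and its interval more than on a p-value. Those are the quantities that a wrong scale corrupts.

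The PRWE raises a smaller question of the same kind: whether the item ratings can produce the stated minimum.

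**Working it through.** **Inputs.** From Secondary outcomes: 30 DASH items, five response levels, score = mean of completed items − 1, stated range 0 to 100; five PRWE pain items rated 1 to 10, ten function items with no rating range given, each subscale out of 50, total out of 100. From Statistical analysis: DASH MCID 10 (5 to 15). Coding of the DASH responses as 1 to 5 is not written out; it is inferred from the subtraction of 1.

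**1. Try to reproduce the stated DASH range.**
- All items at 1: 30/30 − 1 = 0.
- All items at 5: 150/30 − 1 = 4.
- With 27 completed items: 27/27 − 1 = 0 and 135/27 − 1 = 4, so missing items make no difference.

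The range is 0 to 4. The stated 0 to 100 is not reproduced.

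**2. Does the coding matter?** With 0 to 4 coding, the formula gives 0 − 1 = −1 up to 4 − 1 = 3. The width is again 4. Any coding by five consecutive integers spans 4 points, so the conflict does not depend on the inferred coding.

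**3. Find the missing factor.** 100/4 = 25. With 1 to 5 coding, (1 − 1) × 25 = 0 and (5 − 1) × 25 = 100, exactly the stated range.

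**4. Put the MCID on the printed scale.** 10/25 = 0.4, with limits 5/25 = 0.2 and 15/25 = 0.6. The largest possible change on the printed scale is 4, below the MCID of 10 and below its lower limit of 5.

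**5. Effect on the planned test.** Dividing every score by 25 divides the between-group and within-group mean squares by 25² = 625. Their ratio F, and hence the p-value, is unchanged. Means, differences, standard deviations and confidence limits are all divided by 25.

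**6. PRWE floor.** Five pain items rated 1 to 10 give 5 × 1 = 5 to 5 × 10 = 50. For the function subscale, assume the sum of ten items is halved, which brings items with a maximum of 10 to the stated 50.
- Function items 0 to 10: function 0 to 50, total 5 to 100.
- Function items 1 to 10: function 5 to 50, total 10 to 100.
- All items 0 to 10: total 0 to 100.

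With pain items rated 1 to 10, a total of 0 cannot be reached; the maximum of 100 can.

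**The case against.** The best defence is that this is a visible slip with limited reach. The correct range follows immediately, and a scorer who obtained a maximum of 4 would notice. The outer brackets serve no purpose as printed, which suggests a trailing multiplier was lost. Whether the authors or the conversion of the PDF lost it cannot be settled from this text, although nothing there marks a gap. The data forms are in additional files that are not shown, so there is no evidence that the error reached the form or the code. All of this stands, and it limits the severity; it does not make the printed formula right.

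A reader might infer that DASH differences would always look clinically negligible. The document does not support that: it cites the MCID only when saying the trial is not powered for these scores, and it plans no responder threshold or decision rule based on it. Nor would the ANOVA result change.

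A reader might also infer that the PRWE could reach 150, by adding ten unhalved function items rated up to 10 to the pain score of 50. The article rules this out by fixing each subscale at 50 and the worst total at 100. Not spelling out the rescaling is normal condensation in an article, and the function item range is not given at all.

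Even the PRWE floor conflict depends on one phrase. The range sentence speaks of both tests but closes the DASH paragraph, before the PRWE is described; the PRWE paragraph states no minimum. A constant offset would also cancel in change from baseline. The cancellation is not exact if items really run from 1, since the pain subscale then spans 50 − 5 = 45 points instead of 50, but the effect is small.

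**Conclusion.** The DASH scoring rule is wrong as printed. It yields a 4-point scale, contradicts the stated 0 to 100 range and does not fit the quoted MCID. Applied literally, reported DASH means and differences would be too small by a factor of 25. The primary outcome, the sample size and the ANOVA p-values are unaffected. The only inferred input is the 1 to 5 coding, and the width of 4 holds for any five consecutive integer codes. The point deserves correction before data are scored, but it does not threaten the trial's main conclusion.

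The PRWE point is minor and conditional. If the 0 to 100 statement covers both questionnaires, the floor is 5 or 10 instead of 0, depending on the unstated range of the function items. The article does not show whether the item range or the score range is the one in error.

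**What to change.** State the score as DASH = (mean of the completed items − 1) × 25, with items coded 1 to 5. Check the data form and the scoring code against it; scoring one record with all items at 1 and one with all items at 5 should return 0 and 100.

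For the PRWE, say whether the 0 to 100 range is meant to apply to it, and reconcile the item rating range with the stated score range, using the version of the questionnaire on the data form.

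The cost is about two lines of protocol text and a short check of form and code. No design element, sample size or analysis method changes.

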**Method:**

A single centre randomised clinical trial including 120 adults with end-stage isolated wrist arthritis will be performed to compare TWA with and without the CMCJ included in the arthrodesis. The primary outcome is complications in the first post-operative year. Secondary outcomes are Disabilities of the Arm, Shoulder and Hand (DASH) score, Patient Rated Wrist Evaluation (PRWE) and grip strength measured at 1, 2 and 5 years. Late complications, return to work and satisfaction will also be recorded.

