### Participants

Adults aged 18 years and older awaiting TWA will be invited to participate in this trial. Participants will be English speaking, have minimal disability of the upper limb and have non-inflammatory arthritis of the wrist. Additional eligibility criteria are specified in Table 1. The CONSORT statement is followed for the reporting of randomised trials. A participant’s journey through the trial is shown in Fig. 1.

**Table 1 Tab1:** Eligibility and exclusion criteria

Eligibility criteria	
Inclusion criteria	
This study will include English speaking adults aged > 18 years who have been scheduled for total wrist arthrodesis. The conditions which are likely to be included are:	
SNAC (Scaphoid non-union advanced collapse)	
SLAC (Scapholunate ligament advanced collapse)	
Keinbock’s disease/Lunate avascular necrosis	
Preiser’s disease/Scaphoid avascular necrosis	
Wrist osteoarthritis	
Post traumatic arthritis	
Failed partial fusion	
Failed proximal row carpectomy	
Failed ligament repairs	
Exclusion criteria	
Patients will be excluded from this study if they:	
Lack ability to provide informed consent for participation (cognitive capacity or English proficiency)	
Have an inflammatory arthropathy (e.g., Rheumatoid arthritis)	
Have coexisting debilitating other upper limb disorder e.g., rotator cuff tear arthropathy with inability to raise arm above head.	
Neurological dysfunction affecting the limb of interest (CVA, plexus injury, peripheral nerve injury, spasm or contracture)	
Tumour of the wrist (giant cell or other)	
Wrist arthroplasty that will be revised to arthrodesis	
Planned to undergo or have undergone bilateral wrist arthrodesis

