### Baseline data

A timeline for assessment is given in Fig. 1. Initial pre-operative assessment will obtain data on comorbidities, function, clinical assessment of pain at the CMCJ and radiographic assessment with x-ray and computer tomography (CT). Patient reported outcome measures including the DASH and the PRWE will also be administered.

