### Randomisation and blinding

Block randomisation with stratification by surgeon will be used to ensure equal distribution of participants and size of each treatment group in the event that recruitment goals are not achieved. Eligible patients are randomised 1:1 to TWA with CMCJ arthrodesis and spanning plate or TWA without CMCJ arthrodesis with non-CMCJ spanning plate. The randomisation sequence is concealed and administered by an independent non-clinical staff member of the Trauma and Orthopaedic Research Unit at the Canberra Hospital. Letters are then allocated to participating surgeons containing the concealed treatment allocation. In this way the surgeon cannot influence the type of intervention; and the participants, clinical and research staff are blinded.

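### Grip is measured in both hands, but the plan names only ANOVA and never says how the opposite hand's reading is used; naming it as a covariate would give a more precise comparison at little cost

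*Protocol article*

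**What the plan says.** Grip strength is a secondary outcome: "Secondary outcomes will also include patient satisfaction, grip strength and late complications". The Method paragraph of the abstract sets the visits: "Patient Rated Wrist Evaluation (PRWE) and grip strength measured at 1, 2 and 5 years". The measurement covers both hands: "Grip strength will be recorded from three attempts alternating between left and right hands".

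For the analysis, the Statistical analysis section has one general sentence: "Continuous secondary outcomes will be analysed by ANOVA". It names no covariate and no other model term.

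Three other statements bear on the point.

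- The two questionnaires are defined relative to each patient's own starting value ("Secondary outcomes will include changes from baseline DASH and PRWE"). Grip is not defined that way, nor as a ratio to or difference from the other hand.
- The Baseline data section ("Initial pre-operative assessment will obtain data on comorbidities, function, clinical assessment of pain at the CMCJ and radiographic assessment", followed by the questionnaires) does not name grip, so a pre-operative reading may or may not exist.
- Table 1 excludes patients "Planned to undergo or have undergone bilateral wrist arthrodesis", so the opposite wrist is unfused in both arms.

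**The concern.** Grip in kilograms varies widely between people for reasons unrelated to the operation, such as sex, body size and general strength. If operated-hand grip is compared between arms with no adjustment, all of that variation stays in the error term. The opposite hand shares much of it and is measured at the same assessment with the same instrument.

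Precision on grip is worth having here. The Background gives better grip as one argued benefit of keeping the carpometacarpal joint mobile, alongside the ability to make a fist. The trial is sized on complications at that joint, and the Statistical analysis section already concedes that it is not powered for DASH and PRWE. A needlessly wide interval for grip would make it harder to tell whether the argued benefit is real.

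Leaving the grip variable open also allows a later choice between raw kilograms, a difference between hands and a percentage of the other side.

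**Working it through.** **The plan's own figure.** The only sample size stated is 120, based on complication rates that the article does not give, so it cannot be reproduced. No figure is stated for grip. The 120 is used only to obtain the number of patients available.

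**Inputs from the protocol**

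- 120 randomised, 20% dropout, alpha 0.05, beta 0.2 (Sample size).
- Equal allocation: "Eligible patients are randomised 1:1" (Randomisation and blinding).
- Evaluable patients: 120 × 0.8 = 96, or 48 per arm.

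**Assumptions, not in the documents**

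- Two-sided test.
- The 20% loss applies at the visit analysed.
- SD of operated-hand grip within arm: 10 kg, used only to express results in kilograms.
- Within-arm correlation r between the two hands: 0.4 to 0.7.

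**Unadjusted comparison.** Detectable difference = (1.96 + 0.84) × SD × √(2/48) = 2.80 × 0.204 × SD = 0.57 SD, or 5.72 kg at SD 10 kg.

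**Adjusted comparison.** With opposite-hand grip as a linear covariate, the residual variance is multiplied by 1 − r² and the detectable difference by √(1 − r²). The sample-size equivalent is 1/(1 − r²).

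| r | 1 − r² | Variance cut | Detectable difference | Equivalent gain in patients | Power for a 0.5 SD difference |
|---|---|---|---|---|---|
| 0 | 1.00 | 0% | 5.72 kg | none | 69% |
| 0.4 | 0.84 | 16% | 5.72 × 0.917 = 5.24 kg | 1/0.84 = 1.19, so 19% | 76% |
| 0.5 | 0.75 | 25% | 5.72 × 0.866 = 4.95 kg | 1/0.75 = 1.33, so 33% | 81% |
| 0.7 | 0.51 | 49% | 5.72 × 0.714 = 4.08 kg | 1/0.51 = 1.96, so 96% | 93% |

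**Outside that range.** At r = 0.3 the gain is slight: the detectable difference goes from 0.57 to 0.55 SD. At r = 0.8 it goes to 0.34 SD.

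**Simulation check.** With 3,000 simulated trials per value of r and 48 per arm, power for a 0.5 SD difference rose from about 67% to 79% at r = 0.5, and from about 68% to 92% at r = 0.7. The type I error was between 4.6% and 5.5% for both analyses throughout. At r = 0 the power was 69% with or without the covariate, so an uninformative covariate costs almost nothing. The simulation takes the covariate as unaffected by treatment.

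**Why a covariate and not a simple difference.** If the two hands have equal SDs, operated minus opposite has variance factor 2(1 − r): 1.2 at r = 0.4 and 0.6 at r = 0.7. It loses precision when r is below 0.5. The covariate form gives 0.84 and 0.51 at the same values and is never worse, because 1 − r² = (1 − r)(1 + r) and 1 + r does not exceed 2.

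**The case against.** The strongest objection is that nothing wrong has been shown. One general sentence names a family of methods, and a condensed article may leave covariates to an analysis plan that is not at hand. Plain ANOVA of a randomised comparison is unbiased, and the protocol makes no power claim for grip that could be contradicted. This largely stands, and it limits the point to an improvement. It does not remove the point: the article names a method for these outcomes, and a more precise one is available from data already planned.

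A reader might go further and infer that the protocol discards the unoperated hand. The documents do not support that. The grip variable is undefined, and measuring both hands alternately is compatible with a side-to-side measure that could itself be analysed by ANOVA. What can be said is that no use is stated.

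A reader might also infer that adjustment would remove between-person variation. It would only reduce it: at r = 0.4, 84% of the variance remains. Both r and the SD are assumed.

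A further objection concerns the remedy. A reading taken at 1, 2 or 5 years comes after randomisation. Excluding bilateral arthrodesis shows that the other wrist is not fused; it does not prove that the other hand's strength is unaffected by how well the operated hand works, for example through compensatory use. This stands as a stated assumption. A large difference between the two plating methods in the other hand's grip seems unlikely, but the protocol cannot establish that.

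Finally, the other hand may be diseased; the neurological exclusion in Table 1 covers only the limb of interest. That lowers r and shrinks the gain, but does not by itself bias the comparison of arms.

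**Conclusion.** The point holds as a cheap gain in precision. Both hands are measured, the only method named is ANOVA, and no use of the opposite hand's reading is stated. An analysis of operated-hand grip without it would be valid but less precise than it could be. Under the assumed correlations of 0.4 to 0.7, the residual variance would fall by 16% to 49%, and the detectable difference from 5.7 kg to between 5.2 and 4.1 kg at the assumed SD of 10 kg. If the true correlation is near 0.3 or lower, little is gained.

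With a same-visit covariate, the result also rests on the allocated operation leaving the other hand's grip unchanged. This is lost precision on one secondary outcome, with no bearing on the complication outcome or on the 120 participants.

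**What to change.** In the Statistical analysis section, name the grip analysis separately: ANCOVA of operated-hand grip in kilograms, with treatment arm as factor and opposite-hand grip as covariate. Use the pre-operative opposite-hand reading if one is taken, and otherwise the same-visit reading. Include surgeon, as the stratification factor, and whether the operated side is the dominant one if that is recorded. Report the adjusted difference between arms in kilograms with its confidence interval, and the unadjusted difference alongside. Make the change before anyone sees data by arm.

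The cost is one covariate, plus the surgeon and dominance terms, and no new measurement. If the same-visit reading is used, state the assumption that allocation does not affect it; the unadjusted result lets a reader see how much depends on it. A pre-operative reading would avoid that assumption.

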### Radiological evaluation

Routine x-ray and pre-operative CT will be used to assess the integrity of the CMCJ. Intraoperatively fluoroscopy will be used by the surgeon to assess hardware placement, screw length and position, and alignment and rotation of the hand.

Union of the radiocarpal, midcarpal and carpometacarpal joint will be assessed by an independent specialist radiologist at 4–6 months following TWA and be defined as the presence of bridging bony trabeculae.

Non-union will be defined as the absence of bridging trabeculae, with no documented interval change over a 3-month period.

### Data collection

Data will be collected prior to surgery and in the post-operative period by the treating surgeon and at 1,2 and 5 years by blinded subspecialised hand physiotherapists, using standardised data forms (see additional files). These forms will be in locked a filing cabinet.

### Data management

Standardised data forms will be compiled by a researcher blinded to the intervention. Analysis of the data will be performed by a statistician blinded to the treatment. Digitalised data will be stored on a password protected computer.

### Sample size

This study is powered to detect a difference in the rate of complications at the CMCJ. Based on reported complications at the CMCJ in the literature and assuming alpha = 0.05, beta = 0.2 and allowing for 20% drop out, it is expected that 120 participants will be needed to discriminate between the interventions. We plan to recruit patients for this study over 3–4 years.

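### The sample size is powered on complications at the CMCJ, but the primary outcome is any listed complication within 12 months, so the stated 80% power does not apply to the primary analysis

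*Protocol article*

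**What the plan says.** The protocol article names two endpoints and does not connect them.

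- **Sample size:** "This study is powered to detect a difference in the rate of complications at the CMCJ". The error rates (alpha 0.05, beta 0.2), the 20% dropout allowance and the total of 120 follow from literature on complications at that joint. No rates are given.
- **Primary outcome:** "The primary outcome is complication within the 12-month post-operative period. These complications are defined in Table 2". Table 2 opens with "Wound dehiscence" and closes with "Other: medical and surgical". In between it lists infection, fracture, hardware breakage, tendon problems, complex regional pain syndrome and nerve injury. Its non-union entry covers more than the CMCJ: "Non-union: recorded radiocarpal, midcarpal and carpometacarpal joint".
- **Statistical analysis:** "The primary outcome of complications will be analysed by proportional analysis (odds ratio"), with no restriction to the CMCJ.

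The Abstract and the Discussion also give the primary outcome as complications in the first year, without naming the CMCJ. Nothing says that a CMCJ-only analysis is primary, or that the power statement extends to all complications.

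**The concern.** A power statement belongs to one endpoint, one pair of event rates and one test. Here it belongs to a subset of the primary outcome. A reader of the article would naturally take 80% as the chance that the primary odds ratio detects the effect the trial was designed around, and nothing in the text supports that.

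Counting every Table 2 event raises the event rate in both arms. Unless the added events also differ between arms, the contrast is diluted while the binomial variance usually grows. At stake is how the primary result is read: if the interval is wide, readers need to know whether the trial was ever sized for that outcome. The Statistical analysis section already says that the trial is not powered for DASH and PRWE. The primary outcome needs a statement just as clear.

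**Working it through.** **Inputs from the article.** N = 120, 1:1 allocation, alpha 0.05 (taken as two-sided, since the sides are not stated), power 80%, dropout 20%.

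**Evaluable patients.** 120 × (1 − 0.2) = 96, or 48 per arm. Reading the allowance as 120/1.2 = 100, or 50 per arm, changes little.

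**The plan's own figure.** Without event rates, 120 can be neither confirmed nor refuted. What can be found is which CMCJ rates give 80% power at 48 per arm, using the pooled normal approximation:

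power = Φ[(d − 1.96·SE0)/SE1], where d = p1 − p2, SE0 = √(2·p̄(1 − p̄)/48) and SE1 = √((p1(1 − p1) + p2(1 − p2))/48).

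Three such pairs are 5% v 25%, 10% v 33% and 20% v 47%. Check for 5% v 25.24%: d = 0.2024, p̄ = 0.1512, SE0 = 0.0731, SE1 = 0.0701, so (0.2024 − 0.1433)/0.0701 = 0.84 and power = 80%.

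**Moving to the primary outcome.** Assume a non-CMCJ complication risk q that is equal in both arms and independent of CMCJ events. The risk of any complication is then 1 − (1 − p)(1 − q).

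Example with q = 20%: 1 − 0.7476 × 0.8 = 0.402 against 1 − 0.95 × 0.8 = 0.240. Then d = 0.162, p̄ = 0.321, SE0 = 0.0953, SE1 = 0.0938, so (0.1619 − 0.1868)/0.0938 = −0.265 and power = 40%.

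Power for any complication at 48 per arm:

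| CMCJ rates (80% power alone) | q = 10% | q = 20% | q = 30% | q = 40% |
|---|---|---|---|---|
| 5% v 25% | 56% | 40% | 29% | 22% |
| 10% v 33% | 62% | 47% | 36% | 28% |
| 20% v 47% | 67% | 55% | 45% | 36% |

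For 5% v 25%, restoring 80% power under the same assumptions would take a total of about 214, 326, 470 and 664 participants, dropout included.

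**How far this depends on the assumptions.**

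- *No overlap.* If no patient has both kinds of event, the full absolute difference survives. Power for 5% v 25% is then about 63%, 55%, 51% and 51%. At high CMCJ rates (such as 30% v 58%) this extreme case shows no loss.
- *Non-CMCJ events differ in the same direction.* With CMCJ rates of 5% v 25%, a non-CMCJ risk of 10% v 20% gives 1 − 0.95 × 0.90 = 0.145 against 1 − 0.7476 × 0.80 = 0.402, and power of 82%. For 20% v 35% it is 80%. Smaller gaps stay below 80%: 15% v 25% gives 75%, and 20% v 30% gives 68%.

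All event rates in this section are assumptions. None comes from the article.

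**The case against.** The strongest reply is that the loss of power is not shown. The arms differ in more than the handling of the CMCJ: the Intervention subsections describe plates of different make and size, one spanning the joint and one not, and different joint preparation. The Background names non-union, soft tissue irritation and hardware failure as complications of plating, and the Discussion expects those to be evident by 12 months. Several Table 2 items, such as hardware breakage and tendon irritation, could plausibly differ by plate. This stands. Equal non-CMCJ risk is an assumption, and a difference in the same direction could restore the power.

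It does not rescue the power statement. The article does not claim such a difference, and its calculation rests on CMCJ complications alone.

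A second reply is that this is a condensed article. That excuses the missing rates, which are not part of this point. It does not excuse the mismatch, because the article states both endpoints and they differ.

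A reader might also infer from "We choose a superiority study design, with the assumption that treatments are equivalent and set out to test this hypothesis" that a non-significant result would be reported as equivalence. The text does not support that. It declares a superiority design, sets no margin and plans no equivalence test. The sentence is best read as a loosely worded null hypothesis of no difference.

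**Conclusion.** The point holds as a mismatch of endpoints. The 80% power is stated for complications at the CMCJ, while the primary analysis is of any Table 2 complication within 12 months. This follows from the text alone and needs no assumed rate.

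The size is conditional. With equal, independent non-CMCJ risk of 10% to 40%, power at 48 per arm is about 56% to 22% for CMCJ rates of 5% v 25%, and 67% to 36% for 20% v 47%. Other assumptions give a smaller loss or none.

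A reader might conclude that the primary analysis will certainly have far less power, or that a non-significant result is likely. The article gives neither CMCJ nor overall complication rates, so neither conclusion can be drawn.

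**What to change.** Keep n = 120 and do one of the following.

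1. **Align the endpoint.** Make CMCJ complication within 12 months the primary outcome and any complication secondary. The definition must allow the event to occur in both arms. At present, CMCJ non-union is assessed only where that joint was fused, so a definition resting on it could be met in one arm only.
2. **Correct the statement.** Keep any complication as primary, say that the 80% power refers to CMCJ complications only, and give the power or detectable difference for any complication at 48 per arm, with its assumptions.

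The first removes the mismatch. The second discloses it and leaves the power of the primary analysis as it is.

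Neither needs more patients. The first costs a change of wording in the protocol and the registry entry. The second probably means publishing a less favourable power figure.
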